## Abstract

**Introduction:**

Diminished ovarian reserve (DOR) is known to reduce the likelihood of achieving pregnancy or live births in women undergoing *in vitro* fertilization and embryo transfer (IVF-ET). Acupuncture maybe effective for DOR, but current evidence remains limited and inconclusive.

**Methods and analysis:**

This study is a multicenter, randomized, placebo-controlled trial conducted on a large scale. A total of 300 women with DOR preparing for IVF-ET will be randomized 1:1 to acupuncture or placebo acupuncture. Interventions will be administered from the second menstrual cycle preceding the IVF cycle until the day of oocyte retrieval. The primary outcome is the clinical pregnancy rate (CPR) following the first embryo transfer. Secondary outcomes include various IVF-ET indicators, such as the number of follicles ≥ 14 mm, estradiol (E2) levels, and endometrial thickness on the day of human chorionic gonadotropin (hCG) administration; the number of retrieved oocytes, metaphase II (MII) oocytes, and two pronuclei (2PN) fertilizations; as well as the rates of 2PN fertilization, available embryos, high-quality embryos, implantation, cycle cancellation, biochemical pregnancy, pregnancy loss, sustained pregnancy, and live birth. Additionally, ovarian reserve indicators—including antral follicle count (AFC), basal serum levels of follicle-stimulating hormone (FSH), luteinizing hormone (LH), and E2, and anti-Müllerian hormone (AMH)—along with scores from the Self-Rating Anxiety Scale (SAS) will also be evaluated.

**Ethics and dissemination:**

The trial has been approved by the ethics committees of all participating centers. The results will be disseminated in academic journals.

**Clinical Trial Registration:**

http://itmctr.ccebtcm.org.cn/, identifier ID: ITMCTR2024000021.

## Introduction

Diminished ovarian reserve (DOR) is a momentous contributing factor of female infertility, defined by a reduction in oocyte quantity and/or quality, its diagnostic biochemical profile typically includes elevated serum follicle-stimulating hormone (FSH), alongside decreased levels of anti-Müllerian hormone (AMH) and a less antral follicle count (AFC) (1). The pathogenesis of DOR is associated with multiple factors, including age, genetic, iatrogenic, autoimmune, infectious agents, environmental, and social-psychological (2). Epidemiological data from 2004–2011 showed DOR prevalence rising from 19% to 26% (3). DOR usually leads to unsatisfactory outcomes in *in vitro* fertilization-embryo transfer (IVF-ET). DOR patients achieve lower clinical pregnancy rates (CPR) and live birth rates (LBR) during IVF-ET than those without DOR (4, 5).

The subpar response of DOR patients to exogenous gonadotropins poses a major challenge in the field of reproductive endocrinology (6). Elderly individuals and those with elevated basal FSH levels often display poor responsiveness to ovulation induction due to their diminished ovarian reserve (6). Although various interventions, including growth hormone (GH) and dehydroepiandrosterone (DHEA), have shown potential to optimize ovarian performance and reproductive outcomes in assisted reproduction (6–8). Presently, the effectiveness of these treatment modalities has not been definitively confirmed due to insufficient robust clinical trials.

Acupuncture is regarded as a beneficial alternative therapy for DOR (2). Although further high-quality studies are warranted, accumulating evidence demonstrates that acupuncture effectively modulates reproductive hormone profiles (9), enhances ovarian reserve function (10, 11), increases CPR (10, 11), and reduces anxiety (12) in women undergoing IVF-ET. Given these beneficial effects on ovarian reserve parameters and IVF-ET outcomes, acupuncture represents a promising therapy for DOR.

Accordingly, we initiated a prospective, multicenter, randomized controlled trial to rigorously assess both the efficacy and safety of acupuncture for DOR patients undergoing IVF-ET. The primary outcome is the CPR following the first embryo transfer.

## Methods and design

### Study design

This multicenter, randomized, sham-controlled trial aims to compare the effects of verum acupuncture and non-penetrating placebo acupuncture in women with DOR. A target sample of 300 participants will be recruited from 13 Grade A tertiary hospitals strategically distributed across China: three in both East and North China, three in Central China, two in South China, and one each in the Southwest and Northwest. Participating centres are Sichuan Jinxin Xinan Women and Children Hospital, Shaanxi Provincial Hospital of Chinese Medicine, Hainan Women and Children’s Medical Center, Fujian Maternal and Child Health Hospital, General Hospital of Eastern Theater Command, Tianjin Medical University General Hospital, Reproductive and Genetic Hospital of CITIC-Xiangya, Henan Provincial People’s Hospital, The Third Affiliated Hospital of Zhengzhou University, Shanghai University of Traditional Chinese Medicine Affiliated Shuguang Hospital, Shenzhen Maternal and Child Health Hospital, The Seventh Medical Center of the Chinese PLA General Hospital, Beijing Chaoyang Hospital of Capital Medical University.

The study received ethical approval from all participating institutions and was prospectively registered at the International Traditional Medicine Clinical Trial Registry (registration number: ITMCTR2024000021) on 21 February 2024. Participant progression throughout the trial is depicted in the CONSORT-compliant flowchart (**Figure 1**), and key procedural timelines aligned with the SPIRIT checklist are summarized in **Table 1**.

**Figure 1 f1:**
[figure not shown]
Flow diagram of the trial. DOR, diminished ovarian reserve; IVF, *in vitro* fertilization; ICSI, intracytoplasmic sperm injection; COH, controlled ovarian hyperstimulation; ART, assisted reproductive technology; CPR, clinical pregnancy rate; AFC, antral follicle count; AMH, anti-Müllerian hormone; FSH, follicle-stimulating hormone; E2, estradiol; SAS, Self-Rating Anxiety Scale.

**Table 1 T1:** Schedule of recruitment, intervention, and measures.

Time Items	Visit 1	Visit 2	Visit 3	Visit 4	Visit 5
	Screening period (-8 to 0 weeks)	Intervention period (+4 weeks)	Intervention period (+8 weeks)	Intervention period/COH cycle (+10 weeks)	Follow-up (+24 weeks)
Informed consent	**×**				
Inclusion/Exclusion Criteria	**×**				
Demographic data	**×**				
Medical history	**×**				
Treatment history	**×**				
Comorbidities	**×**				
Acupuncture/Placebo acupuncture		**×**	**×**	**×**	
AFC	**×**			**×**	
FSH, LH, E2	**×**			**×**	
AMH	**×**			**×**	
SAS	**×**			**×**	
IVF/ICSI				**×**	
Pregnancy outcomes					**×**
Concomitant medication		**×**			
Adverse event		**×**			

COH, controlled ovarian hyperstimulation; AFC, antral follicle count; FSH, follicle-stimulating hormone; LH, luteinizing hormone; E2, estradiol; AMH, Anti-Mullerian hormone; SAS, Self Rating Anxiety Scale; IVF, *in vitro* fertilization; ICSI, intracytoplasmic sperm injection.

### Participants

Potential participants will be identified by dedicated clinicians through hospital-based advertisements (printed posters, WeChat official accounts, and approved online platforms). Before enrollment, a qualified clinician will administer a detailed briefing to each eligible participants, covering the trial’s objectives, methodology, procedures, anticipated benefits, and potential risks. Written informed consent will be formally documented from all participants prior to the initiation of any trial-related activities.

#### Inclusion criteria

Women meeting the diagnostic criteria for DOR (13) and scheduled for IVF-ET will be enrolled provided they fulfill all the following conditions:

Age 20–39 years;AFC<5, AMH<1.2 ng/mL (13);With regular menstrual cycles (21–35 days);With GnRH antagonist or microstimulation protocol for controlled ovarian hyperstimulation (COH);Plan to transfer 1–2 high-quality cleavage embryos or one blastocyst;Able and willing to give written informed consent.

#### Exclusion criteria

We will exclude individuals meeting any of the following criteria:

Basal FSH ≥ 25 IU/L;Congenital malformations of the reproductive tract; untreated endometrial polyps, intrauterine adhesions, active uterine infection, or hydrosalpinx; endometrial thickness < 7 mm on the HCG trigger day; submucosal fibroids > 5 cm in diameter; or any stage of endometriosis;Repeated implantation failure, defined as failure to achieve clinical pregnancy after ≥2 fresh or frozen ET cycles with the transfer of ≥4 top-grade cleavage embryos or ≥2 high-quality blastocysts;Hyperprolactinaemia, hyperandrogenism, thyroid dysfunction, chronic adrenal insufficiency, or any other endocrine or metabolic disorder that has not been normalized with standard therapy;Male partner with azoospermia;Severe cardiovascular, cerebrovascular, hepatic, renal, malignant, haematological, or psychiatric disease;Acupuncture for infertility within the preceding 3 months;Recurrent pregnancy loss, defined as ≥ 3 consecutive spontaneous miscarriages < 28 weeks’ gestation with the same partner;Clinically significant anxiety, indicated by a Self-Rating Anxiety Scale (SAS) score > 70;Chromosomal abnormalities in either partner.

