#### Randomization method

Randomization will be performed after obtaining informed consents. A secure online computerized randomization system will be utilized for randomization to ensure allocation concealment. This centralized web-based platform incorporates multiple functional modules for randomization, data entry, and management, and will be overseen by an independent statistical team. Qualified participants will be assigned to the acupuncyure or placebo acupuncyure groups in a 1:1 allocation ratio, employing stratified block randomization by age (< 35 years vs. ≥ 35 years) through a computer-generated system. Upon enrollment of eligible subjects, personnel responsible for randomization will log into the central randomization system via the internet to obtain a randomization number.

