#### Secondary outcomes

The secondary outcomes include the number of follicles ≥ 14 mm, E2 level, and endometrial thickness on the hCG trigger day; the number of retrieved oocytes, metaphase II (MII) oocytes, and two pronuclei (2PN) fertilizations; as well as the rates of 2PN fertilization, available embryos, high-quality embryos, implantation, cycle cancellation, biochemical pregnancy, pregnancy loss, sustained pregnancy, and live birth. The outcomes of IVF-ET and their definitions are summarized in **Table 4**. While the post-treatment observation will be terminated at about 24 weeks, data on live birth will be obtained through the participating centers’ mandatory, complete follow-up system extending to the end of pregnancy.

**Table 4 T4:** Diagnosis definitions of IVF-ET outcomes.

Diagnosis	Definition
Primary outcomes	
clinical pregnancy rate (CPR)	the number of clinical pregnancies divided by the total number of embryo transfer cycles.
Secondary outcomes	
Outcomes of IVF-ET	
2PN fertilization rate	the number of 2PN embryos divided by the number of MII oocytes
available embryo rate	the number of transferable embryos divided by the number of 2PN fertilization
high-quality embryo rate	the number of high-quality embryos divided by the number of normally fertilized cleavage embryos. High-quality embryos were defined based on the day of embryo transfer, according to the Istanbul consensus and Gardner criteria, as follows: Day 2: embryos with 4 cells, <10% fragmentation, and absence of multi-nucleation; Day 3: embryos with 8 cells, <10% fragmentation, and no multi-nucleation; Day 5: blastocysts at stage 4, with inner cell mass and trophectoderm both graded as A (17, 18).
Implantation rate	the number of gestational sacs divided by the number of embryos transferred.
cycle cancellation rate	the number of cancelled embryo transfer cycles divided by the number of embryo transfer cycles
biochemical pregnancy rate	the number of patients with positive serum b-hCG pregnancy test results divided by total embryo transfer cycles
pregnancy loss rate	the number of pregnancy termination cycles within 12 weeks divided by the number of embryo transfer cycles
sustained pregnancy rate	the number of cycles of pregnancy greater than 12 weeks divided by the number of embryo transfer cycles
live birth rate	the number of live births divided by total embryo transfer cycles.
Scale measurement	

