Furthermore, the predominant number of individuals diagnosed with DOR manifest symptoms of anxiety to varying extents. The utilization of the SAS, a tool specifically developed to gauge anxiety and psychological stress, will serve to evaluate the levels of anxiety present in DOR women (30).

Acupuncture has been shown to modulate gonadotropin levels, lowering FSH, LH, and the FSH/LH ratio, while elevating E2 and ameliorating emotional symptoms in DOR patients, with a favorable safety profile (9–11). Research indicated that acupuncture contributes to higher CPR in IVF-ET for DOR women by effectively improving their underlying ovarian reserve function (31). Another investigation demonstrated that acupuncture positively influences hCG-day estrogen levels, endometrial conditions, thereby improved endometrial receptivity during IVF-ET (32). However, existing trials are limited by small sample sizes. This large-sample, multicenter RCT is designed to definitively assess the efficacy and safety of the acupuncture intervention, thereby addressing this critical evidence gap.

According to traditional Chinese medicine (TCM) theory, an imbalance of the Ren Meridian (Conception Vessel, CV) and Chong Meridian (Penetrating Vessel, PC) constitutes a fundamental pathogenesis of DOR, and is associated with kidney deficiency, liver stagnation, and spleen deficiency. Therefore, the main therapeutic principles for DOR involve regulating the Chong and Ren Meridians, tonifying the kidney, regulating the liver and fortifying the spleen. During this clinical trial, the selected acupuncture points will include CV 12 (Zhongwan) and CV 4 (Guanyuan) from the Ren Meridian; KI 12 (Dahe) and KI 16 (Huangshu), which are intersection points of the Kidney Channel of Foot-Shaoyin and the Chong Meridian; SP 6 (Sanyinjiao), which serves to invigorate the kidney, regulate the liver, and fortify the spleen; BL 23 (Shenshu), BL 33 (Zhongliao), and KI 3 (Taixi), which are utilized to reinforce the kidney and nourish the essence; and LR 3 (Taichong), which alleviates liver tension and harmonizes qi.

The methodological rigor of this trial, particularly regarding randomization, allocation concealment, and blinding across all study stages, will be safeguarded by the use of placebo needles, adhesive pads, and an EDC system.

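### The exclusion for a thin endometrium on the hCG trigger day cannot be assessed before randomisation, duplicates a secondary outcome and conflicts with the ITT principle

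*Protocol article*

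**What the plan says.** The Exclusion criteria section opens with "We will exclude individuals meeting any of the following criteria". Among the uterine conditions it lists "endometrial thickness < 7 mm on the HCG trigger day".

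Table 1 ticks the inclusion and exclusion check at Visit 1 only (screening, weeks -8 to 0). On timing, the Randomization method section says "Randomization will be performed after obtaining informed consents" and then "Upon enrollment of eligible subjects, personnel responsible for randomization will log into the central randomization system". Under Acupuncture group, treatment runs three times a week for roughly ten weeks, up to oocyte retrieval. Table 1 places the stimulation (COH) cycle at Visit 4, +10 weeks. The COH regimen section lets stimulation begin early only if at least 8 weeks of pretreatment are complete.

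The Secondary outcomes section then states: "The secondary outcomes include the number of follicles ≥ 14 mm, E2 level, and endometrial thickness on the hCG trigger day". The Discussion cites an investigation reporting that "acupuncture positively influences hCG-day estrogen levels, endometrial conditions". The Statistical analysis section applies the intention-to-treat principle to every analysis.

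**The concern.** An exclusion criterion has to be known before a woman is randomised. This one is read in the stimulation cycle, late in the allocated treatment. A site that follows the list literally would declare a randomised woman ineligible because of a value observed under treatment.

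That would matter in three ways:

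- The women left in each arm would be selected on something treatment may have changed, so the arms would no longer be comparable by design.
- The trigger-day thickness outcome would lose its lower end in both arms, because no value under 7 mm would remain.
- The exclusion list and the ITT statement would give opposite instructions for the same woman, and 13 centres might not resolve this the same way.

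**Working it through.** **Order of events.** The protocol article gives no figure for this point to reproduce, so the check sets its sections side by side.

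| Step | Where stated | When |
|---|---|---|
| Eligibility check | Table 1, Visit 1 | weeks -8 to 0 |
| Randomisation of eligible women | Randomization method | on enrolment, before allocated treatment can start |
| Allocated treatment | Acupuncture group | about 10 weeks, to oocyte retrieval |
| Earliest COH start | COH regimen | after at least 8 weeks of treatment |
| COH cycle | Table 1, Visit 4 | about +10 weeks |
| Trigger-day thickness | Exclusion criteria; Secondary outcomes | within the COH cycle |

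At three sessions a week, at least 8 × 3 = 24 of about 30 sessions are scheduled before stimulation may start. The trigger day is later still. The criterion therefore cannot be met or failed at Visit 1 if it refers to the trial cycle, and no section ties it to another cycle.

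**Possible effect on the primary comparison.** The share of women below 7 mm and their clinical pregnancy rate (CPR) are not in the documents. Everything about them below is assumed. If an arm has overall CPR p, a share f is removed, and the removed women have CPR t, the remaining CPR is (p − f·t)/(1 − f).

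*No true effect, p = 22% in both arms (the Sample size section's placebo rate):*

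| Removed, acupuncture / placebo | t | Acupuncture | Placebo | Difference (points) |
|---|---|---|---|---|
| 5% / 10% | 10% | 0.215/0.95 = 22.6% | 0.210/0.90 = 23.3% | −0.7 |
| 5% / 15% | 10% | 0.215/0.95 = 22.6% | 0.205/0.85 = 24.1% | −1.5 |
| 5% / 15% | 0% | 0.220/0.95 = 23.2% | 0.220/0.85 = 25.9% | −2.7 |
| 10% / 20% | 5% | 0.215/0.90 = 23.9% | 0.210/0.80 = 26.3% | −2.4 |

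*Planned effect, 38% vs 22% (+16.0 points):* the same four rows give +16.1, +15.4, +14.1 and +15.4. For example, in the second row 0.375/0.95 = 39.5% and 39.5 − 24.1 = 15.4.

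*Direction.* These rows assume that fewer women are thin under acupuncture. If the shares are swapped, the signs in the no-effect table reverse. With equal shares (10% in each arm, t = 5%) there is no distortion under no effect, since both arms become 0.215/0.90. At the planned effect the contrast rises to 0.375/0.90 − 0.215/0.90 = 41.7 − 23.9 = +17.8 points.

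**Possible effect on power.** The normal approximation with pooled variance for 38% vs 22%, two-sided 0.05, gives 77.5% power at the stated 120 per group. (It needs 128 per group for 80%. That is a separate matter and does not affect this point.) If a further 5%, 10%, 15% or 20% of the 120 were removed, leaving 114, 108, 102 or 96, power would be 75.4%, 73.1%, 70.6% or 67.9%. This holds the two rates fixed, which is a simplification.

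**The case against.** *Removal is not stated.* No section describes withdrawing a randomised woman, or dropping her from an analysis, for a thin endometrium. Table 1 has no second eligibility check at Visit 4, and the ITT statement would keep her. This stands. A reader might infer that such women will be removed from the analysis. The documents support only the conditional: if the listed criterion is applied, it conflicts with ITT.

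*An earlier cycle may be meant.* The item sits among uterine conditions known at screening, and Visit 1 records treatment history. The reading is possible, but the text does not say it. Other items in the list state their look-back, such as acupuncture in the previous 3 months. The wording here matches the secondary outcome, and a woman with no earlier cycle would have no value. If this was the intention, the text still needs correcting.

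*The rule could reverse the result.* A reader might infer this, and a case can be built. Assume 80% of women are never thin (CPR 25%), 10% are thin only without acupuncture (8% control, 15% acupuncture) and 10% are always thin (8%). All randomised give 22.3% vs 21.6%, or +0.7 points. After exclusion the rates are (0.20 + 0.015)/0.90 = 23.9% vs 25.0%, or −1.1. The reversal depends on assuming almost no true effect. Keep the strata but set the acupuncture arm to the planned 38%: the contrast goes from 38.0 − 21.6 = +16.4 to (0.38 − 0.008)/0.90 − 0.25 = 41.3 − 25.0 = +16.3. The documents do not support a claim of reversal.

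*The Discussion does not mention thickness.* Correct. It cites one investigation on hCG-day estrogen and endometrial conditions. That makes a treatment effect on thickness plausible to the authors, but it does not assert one.

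**Conclusion.** The point holds as an error in the eligibility rule as written. The timing conflict, the overlap with a secondary outcome and the clash with ITT all follow from the text and need no assumption beyond reading the criterion as referring to the trial cycle.

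The consequences are conditional. Applied as written, the rule would select randomised women on a variable that treatment may affect and would cut the thickness outcome off at 7 mm. The size and direction of any bias in CPR cannot be determined from the documents. With 5% and 15% removed, by assumption, the distortion is about 1.5 to 2.7 points near the null. At the planned effect the assumed scenarios with unequal shares leave 14.1 to 16.1 of the 16 points, a small change relative to that effect. The stated ITT principle limits the harm if it prevails over the exclusion list, but the article does not say which prevails.

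**What to change.** Reconcile Table 1, Exclusion criteria, Randomization method, Secondary outcomes and Statistical analysis in one short amendment:

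- Remove the trigger-day item from the exclusion list, or tie it to a value known before randomisation and say what applies when a woman has none.
- State that no randomised woman is excluded from the ITT analysis because of her trigger-day thickness. This partly repeats the existing ITT sentence, but it settles which text governs.
- Report trigger-day thickness without a cut-off at 7 mm.

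Whether a transfer goes ahead remains a clinical decision and is not touched. A reader might also want women without a transfer counted as not pregnant. That would change the denominator of the primary outcome, which is embryo transfer cycles, and is a separate matter.

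The cost is a text amendment with no extra visits. The downside is that some women with a thin endometrium stay in the analysis and may slightly lower the rates in both arms.

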#### Randomization method

Randomization will be performed after obtaining informed consents. A secure online computerized randomization system will be utilized for randomization to ensure allocation concealment. This centralized web-based platform incorporates multiple functional modules for randomization, data entry, and management, and will be overseen by an independent statistical team. Qualified participants will be assigned to the acupuncyure or placebo acupuncyure groups in a 1:1 allocation ratio, employing stratified block randomization by age (< 35 years vs. ≥ 35 years) through a computer-generated system. Upon enrollment of eligible subjects, personnel responsible for randomization will log into the central randomization system via the internet to obtain a randomization number.

